## 2. Methodology

### 2.1. Trial Design and Setting

A parallel-group, single-blinded, two-arm randomized controlled superiority trial compares the effectiveness of HRTP to TAU with a 1:1 allocation ratio. Quantitative and qualitative data will be used to examine the effect of HRTP on racial trauma, depression (primary outcomes), and functioning (secondary outcomes). The trial will take place in an urban city in the province of Ontario, Canada.

Conducting the study in Ottawa contributes to the generalizability of the findings due to the city’s demographic and cultural diversity. As Canada’s capital, Ottawa attracts individuals from across the country and around the globe, providing a considerable mix of racial, ethnic, and linguistic communities. Based on the 2021 Population Census, Black people represented the largest racialized group at 8.5%, while Arabs and South Asian people each represented 5.8% of the total population of the city (Statistics Canada, 2021). As of 2021, there are also some 46,500 Indigenous people living in the Ottawa area, making up 3.2% of the population (Statistics Canada, 2021). This diversity means that the study is more likely to capture a range of lived experiences, cultural contexts, immigration histories, and socioeconomic backgrounds, thereby strengthening the external validity of the findings. A broad and varied participant pool will help ensure results are applicable to other urban centres and potentially even to more rural or international settings that share similar multicultural characteristics.

This study will follow the ethical principles of the Canadian Code of Ethics for Psychologists (CPA, 2017) and the Ethical Conduct for Research Involving Humans (TCPS-2, 2014). Informed consent will be obtained from all participants. The pilot study has been approved by the Research Ethics Board (H-02-22-7613) of the University of Ottawa, ensuring the protection of participant privacy and confidentiality. Participants may withdraw from the study at any time without consequence.

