### 1.4. The Goals of the Current Study

The primary objective of this paper is to describe a randomized controlled trial that will compare the efficacy of the HRTP for people of colour suffering from racial trauma compared to a control condition of treatment-as-usual (TAU) in reducing the severity of racial trauma and related symptoms, as well as improving functioning. This paper will provide preliminary feasibility evidence in terms of implementation, practicality, and acceptability for clients and therapists. Additionally, we will outline methodological approaches to trial design, the research population, and treatment protocols. That is, methodological approaches which could serve as inclusive and viable models for engaging in clinical research related to racialized populations. Specifically, the proposed trial will examine: (a) whether the administration of the HRTP will result in a clinically significant reduction in racial trauma symptoms in participants compared to the TAU control group, and (b) whether any clinically significant reduction in racial trauma symptoms is maintained long-term (i.e., 4 months after the intervention).

It is hypothesized that the completion of the 12-session HRTP will result in a clinically significant improvement in participants’ racial trauma symptoms and severity, as well as improved functioning. It is also hypothesized that these changes will be greater than changes in the control conditions and will be maintained 4 months following the completion of the intervention.

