### 2.8. Study Measures

The study measures included in the trial are two intake measures, three primary outcome measures, and two secondary outcome measures. Before study admission, two intake measures will be administered to prospective participants. These measures will be used to assess if prospective participants meet the study’s inclusion criteria and to better understand the participants’ mental health profiles.

The *Mini International Neuropsychiatric Interview* (MINI 7.0.2; Sheehan et al., 1998) is a semi-structured diagnostic interview designed to briefly assess 17 of the most common mental disorders according to the *Diagnostic and Statistical Manual of Mental Disorders, Fifth Edition* (DSM-5) criteria. The modules assessed include major depressive episodes, suicidality, manic and hypomanic episodes, panic disorder, agoraphobia, social phobia, obsessive–compulsive disorder, post-traumatic stress disorder, alcohol use disorder, substance use disorder, psychotic disorders and mood disorders with psychotic features, anorexia nervosa, bulimia nervosa, binge eating disorder, and generalized anxiety disorder, among others. The MINI was initially created for cross-cultural application and has since been adapted for use in several languages and diverse populations worldwide (e.g., Churbaji et al., 2020; Eytan et al., 2007).

The *University of Connecticut Racial/Ethnic Stress & Trauma Survey* (UnRESTS; Williams et al., 2018a) is a semi-structured diagnostic interview for assessing racial trauma. It consists of several parts, including probes around an individual’s racial and ethnic identity development, experiences of direct overt racism, experiences of racism by loved ones, experiences of vicarious racism, and experiences of covert racism (or microaggressions). The interview concludes with a 29-item checklist which assesses whether an individual’s racial trauma satisfies a DSM-5 diagnosis for PTSD. To render a racial trauma diagnosis (Williams & Zare, 2022), an individual must satisfy the criteria for a minimum of three of the four PTSD symptom clusters as per the checklist (i.e., re-experiencing, avoidance, negative changes in cognition and mood, and physiological arousal and reactivity). The said symptoms must also be clinically significant and must have been present for a month or more.

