### 2.10. Secondary Outcomes

Two secondary outcomes will also be measured at three time points within the treatment group only (weeks 4, 8, and 12). See Table 1 for the participants’ assessment schedule.

The *Helping Alliance Questionnaire* (HAq-II; Luborsky et al., 1996) is a 19-item clinical measure which asks respondents to consider their relationship with their therapist, and rate items according to how strongly they agree or disagree. Sample items include “I feel I am working together with my therapist in a joint effort” and “The therapist and I make unprofitable exchanges”. Items are rated on a 6-point scale, where “1” is strongly disagree and “6” is strongly agree. A total score is calculated from a sum of all items (with some items requiring reverse scoring first). Higher scores are indicative of a better-quality therapeutic alliance between the respondent and the therapist, as perceived by the respondent. The HAq-II has a test–retest reliability over a three-session span of 0.78. It has previously been tested with African American adult clients in a substance use treatment setting, finding comparable conceptualizations of the therapeutic alliance (Dillon, 2013).

The *Racial Microaggressions in Counselling Scale* (RMCS; Constantine, 2007) is a 10-item clinical measure designed to assess the occurrence of subtle covert expressions of prejudice or racism (i.e., microaggressions) within the therapeutic setting as perceived by the respondent/client. Sample items include “my counsellor avoided discussing or addressing cultural issues in our session(s)” and “my counsellor sometimes seemed unaware of the realities of race and racism”. Items are rated on a 3-point scale where “0” is this never happened and “2” this happened and I was bothered by it. An RMCS total is obtained by summing all item ratings together, with higher total scores suggestive of more microaggressions being observed within the therapeutic setting. The RMCS was developed for and tested within diverse ethnoracial groups.

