The secondary outcomes will compare the quality of the therapeutic experiences throughout the treatment group (HRTP therapy; weeks 4, 8, 12), as well as comparing the quality of the sessions between the treatment and control groups (week 12). The strength of the therapeutic alliance between the participants and therapists (Helping Alliance Questionnaire; Luborsky et al., 1996) will be evaluated, as will whether or not the participants perceived any microaggressions in their sessions (Racial Microaggressions in Counselling Scale; Constantine, 2007).

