## Figures and Tables

**Figure 1 behavsci-15-00856-f001:**
[figure not shown]
Participant flow diagram in HRTP Trial.

**Table 1 behavsci-15-00856-t001:** Participant assessment schedule.

Time	Session	Week	Measures	
			Intervention Group	Control/TAU Group
T1	Intake	0	MINI; UnRESTS; BDI-II; RTS; TSDS	
T2	4	4	BDI-II; RTS; TSDS; HAq-II; RMCS	nothing
T3	8	8	BDI-II; RTS; TSDS; HAq-II; RMCS	nothing
T4	12	12	BDI-II; RTS; TSDS; HAq-II; RMCS	BDI-II; RTS; TSDS; HAq-II; RMCS
T5	Follow Up	28	BDI-II; RTS; TSDS	participants will have withdrawn from the study or started the protocol

Note. BDI-II: Beck Depression Inventory-II; HAq-II: Helping Alliance Questionnaire-II; MINI: The Mini International Neuropsychiatric Interview; RMCS: Racial Microaggressions in Counselling Scale; RTS: Racial Trauma Scale; TSDS: Trauma Symptoms of Discrimination Scale; UnRESTS: University of Connecticut Racial/Ethnic Stress & Trauma Scale.

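### Functioning is a hypothesis and the named secondary outcome, but no listed instrument measures it; the schedule and general model for the two scales in its place also need reconciling

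*Protocol article*

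**What the plan says.** **Functioning.** The abstract, the objective in Section 1.4 and the opening of the Discussion all name better functioning as something the trial will evaluate. The hypothesis in Section 1.4 predicts improvement in "racial trauma symptoms and severity, as well as improved functioning", and goes on to say that "these changes will be greater than changes in the control conditions and will be maintained 4 months following the completion of the intervention". Section 2.1 assigns the outcome roles: "racial trauma, depression (primary outcomes), and functioning (secondary outcomes".

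**Instruments.** Section 2.8 counts the measures: "two intake measures, three primary outcome measures, and two secondary outcome measures". Sections 2.8 to 2.10 name and describe each one, and Table 1 schedules the same set. The secondary pair in Section 2.10 is the HAq-II (the client's view of the alliance with the therapist) and the RMCS (microaggressions the client perceived in therapy).

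**Schedule of the secondary pair.** Section 2.10: "Two secondary outcomes will also be measured at three time points within the treatment group only (weeks 4, 8, and 12". Table 1 gives both arms the same week-12 pack, "BDI-II; RTS; TSDS; HAq-II; RMCS". Neither scale appears in the week-0 or week-28 packs.

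**Analysis.** The first paragraph of Section 2.12 puts primary and secondary outcomes, therapeutic experiences included, into a two-way mixed ANOVA: time (pre-test, post-test and possibly follow-up) by condition (HRTP, control). The last paragraph of Section 2.12 gives the secondary outcomes their own analyses: a look across weeks 4, 8 and 12 within HRTP, and "comparing the quality of the sessions between the treatment and control groups (week 12".

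**The concern.** A hypothesis that is comparative and extends to follow-up needs an instrument, a baseline, a control measurement and a late measurement. Functioning has none of these. At reporting, the team would have to drop the hypothesis silently, claim better functioning from symptom scores, or let alliance and microaggression scores stand in for a patient outcome they do not measure.

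Two smaller problems affect the scales that do fill the secondary slot. If site staff follow the text of Section 2.10, the TAU arm never completes HAq-II or RMCS. The only control data for the week-12 comparison are then lost and cannot be recovered later. If the analyst follows the general sentence in Section 2.12, the model asks for time points at which these scales are not collected.

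**Working it through.** The point rests on no stated figure, so there is none to reproduce. The check is a count of instruments and of arm-by-time cells.

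**Step 1: instruments against the construct.** 2 intake + 3 primary + 2 secondary = 7.

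| Instrument | Role | What the article says it captures |
|---|---|---|
| MINI | intake only | psychiatric diagnoses |
| UnRESTS | intake only | racial trauma diagnosis |
| RTS | primary | severity of trauma symptoms due to racism |
| BDI-II | primary | severity of depressive symptoms |
| TSDS | primary | distress from discrimination |
| HAq-II | secondary | therapeutic alliance |
| RMCS | secondary | microaggressions in therapy |

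Described as a measure of functioning: 0 of 7.

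**Step 2: HAq-II and RMCS data against the mixed ANOVA of Section 2.12.** Cells required = time levels × 2 arms.

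| Time levels | Cells required | Filled under Table 1 | Filled under Section 2.10 read literally |
|---|---|---|---|
| weeks 0, 12 | 2 × 2 = 4 | 2 (week 12, both arms) | 1 (week 12, HRTP) |
| weeks 0, 12, 28 | 3 × 2 = 6 | 2 (week 12, both arms) | 1 (week 12, HRTP) |

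Only one of the required time levels is ever observed. Neither a time effect nor a Condition × Time interaction can be estimated. Under the literal Section 2.10 there is no control observation either, so no condition effect can be estimated.

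Redefining time as weeks 4, 8 and 12 does not rescue the model. Table 1 would fill 3 (HRTP) + 1 (TAU) = 4 of 6 cells, and a single TAU time point still gives no interaction. A week-0 value is not available in principle: under Section 2.4 a therapist is assigned only after intake, and both scales ask about the therapist.

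**Step 3: the same data against the last paragraph of Section 2.12.**

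- Within HRTP over weeks 4, 8 and 12: 3 of 3 cells filled under either reading. Feasible.
- HRTP against TAU at week 12: 2 of 2 cells under Table 1, 1 of 2 under the literal Section 2.10. Feasible only if Table 1 governs.

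**The case against.** **On functioning.** The article may condense a fuller protocol. Section 2.1 mentions qualitative data, and the RTS has a subfactor on difficulty coping. Functioning also appears in neither of the two questions that Section 1.4 lists for examination, nor in the predictions of Section 2.12, nor in the sample size basis of Section 2.2.

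The last part stands: the primary comparison and its sizing do not depend on functioning. The rest does not remove the gap. Section 2.8 gives a counted list, and Section 2.10 fills the secondary slot with other constructs, so this is a mismatch within the article and not an abbreviated detail. No qualitative assessment of functioning is described. The coping subfactor belongs to a primary symptom scale whose higher scores are said to mean more distress, and the article nowhere designates it as functioning. The two interviews are given once, at intake, and cannot show change.

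**On the secondary scales.** A reader might infer that HAq-II and RMCS cannot be analysed at all, or that the trial has no workable secondary analysis. The article does not support that. The last paragraph of Section 2.12 sets out two suitable comparisons, Table 1 schedules the data for both, and Section 2.2 already names an independent-samples t-test. The sentence in Section 2.10 can also be read as limiting the three time points, and not all measurement, to the treatment group, and the section then refers to Table 1. So this limb is a matter of reconciling text. The literal wording still conflicts with two other places, and the general ANOVA sentence still covers scales it cannot handle.

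**Conclusion.** The point holds in three parts of unequal weight.

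1. **Main part.** Functioning is an aim, a hypothesis and the named secondary outcome, and 0 of 7 instruments is described as measuring it. The hypothesis of a gain greater than control and maintained at 4 months cannot be tested as the article stands.
2. **Minor.** Section 2.10 contradicts Table 1 and the last paragraph of Section 2.12 on whether TAU completes HAq-II and RMCS at week 12.
3. **Minor.** The pre-test, post-test and follow-up mixed ANOVA cannot be fitted to these two scales: at most 2 of 4, or 2 of 6, required cells hold data, all at week 12. The two comparisons given specifically for them are feasible if Table 1 governs.

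This should be corrected, but it does not threaten the primary analysis. The verdict assumes that the counted list in Section 2.8 and the schedule in Table 1 are complete. A functioning measure in an unseen fuller protocol would still leave the article's list to be corrected.

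**What to change.** **Functioning: choose one.**

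- Add one brief validated self-report functioning scale to the week 0 and week 12 packs in both arms. Add it at week 28 in HRTP if maintenance is claimed. With weeks 0 and 12 in both arms, the existing Condition × Time model applies. Since TAU has no week-28 assessment, maintenance would be a within-HRTP statement and superiority a week-12 one. Cost: a few minutes of questionnaire time per visit, at two visits (three in HRTP with week 28).
- Or remove functioning from the abstract, objective, hypothesis, Section 2.1 and Discussion, and name alliance and perceived microaggressions as the secondary outcomes in Section 2.1. Cost: wording only.

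**Schedule.** Reword Section 2.10 so that HAq-II and RMCS are taken at weeks 4, 8 and 12 in HRTP and at week 12 in TAU, as in Table 1. Cost: one sentence, to be settled before TAU participants reach week 12.

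**Analysis.** In Section 2.12, exclude HAq-II and RMCS from the mixed ANOVA and analyse them only by the comparisons already in its last paragraph: within HRTP over weeks 4, 8 and 12, and between arms at week 12. Cost: one sentence, with no new data.

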### 2.2. Sample Size, Randomization, and Allocation

A sample of 96 participants (48 per group) is needed for an 80% probability to identify a difference between the treatment and control group. The power analysis for the sample size estimation was based on the means, standard deviations, and clinical cut-off for the primary outcomes (RTS, TSDS; Williams et al., 2022c, 2023b). Drawing on previous research, we hypothesized a standard mean difference of between 0.36 and 0.52, between the treatment and control group, which translates to a 10–20% decrease in the primary outcomes (i.e., RTS, TSDS) for individuals at the endpoint of treatment. Given these effect estimates, with an alpha of 0.05, an 80% power, and a 20% attrition, we estimated a sample size of approximately 96 (48 per group) will be needed. This randomized controlled trial will use an ANOVA and t-test (alpha error level = 5%, two-sided) for independent samples.

This sample size will require tailored recruitment efforts, community partnerships, and culturally safe retention strategies throughout the trial. Given differential attrition rates for racialized communities, the research team will spend additional time at intake discussing barriers to participation, issues with attendance, and address any participant concerns. Additionally, the research team will offer flexible session meeting times (e.g., evenings and weekends), and telephone check-ins as needed. The research team shall also compensate participants for both their completed sessions and batteries of measures.

In terms of blinding, the trial research team will be unaware of the group allocation. This includes the principal investigator and project coordinator who are overseeing the trial implementation, research assistants who will support recruitment and data collection, and the statistician conducting the analysis. See Figure 1 for the participant flow diagram of the trial.

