On therapist adherence to the assigned protocol, within the pilot study (*n* = 14 client cases which included 10 completers and 4 early dropouts) 71.4% of sessions in the Stabilization phase, 66.7% in the Healing phase, and 62.5% in the Empowerment phase required no deviation on the part of therapists to meet client needs. Moreover, it is important to note, many of the deviations reported related to either (i) allocating more or less time to an existing protocol agenda item than was suggested in the protocol; or (ii) rearranging protocol agenda items to better fit the natural flow of the session. Few of the deviations reported included the therapist feeling obligated to look beyond the protocol or introduce non-HRTP interventions to meet client needs (between 9.5 and 17.6%, depending on the treatment phase). On the matter of client homework completion, clients in the pilot study had a completion rate of 51.2% in the Stabilization phase, 56.9% in the Healing phase, and 62.5% in the Empowerment phase. There was also an additional 12.2%, 35.3%, and 32.5% partial completion rate for the different phases, respectively.

Conversely, *acceptability* is defined as the perception of the new treatment by implementation stakeholders (Bowen et al., 2009). As such, acceptability was operationalized in terms of (1) therapist comfort with delivering the protocol, as well as (2) client satisfaction with the HRTP. On therapist comfort, part of each session note reflection required therapists to rate their level of comfort in terms of delivering the session material on a 5-point scale: “1—extremely uncomfortable”, “2—slightly uncomfortable”, “3—neither comfortable or uncomfortable”, “4—slightly comfortable”, or “5—extremely comfortable”. And finally, as an element of each client’s week 20 data collection (note, within the pilot study we conducted follow-up at 20 weeks, not 28), clients were asked “If you had a family member or close friend that suffered from racial trauma, would you recommend they complete the HRTP. Why or why not?”.

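### The stated inputs do not give 96 participants: at 96 randomised with 20% attrition, power for an SMD of 0.36 to 0.52 is about 34% to 61%, not 80%

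*Protocol article*

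**What the plan says.** All inputs stand in one paragraph of section 2.2 (Sample Size, Randomization, and Allocation).

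- Target: "A sample of 96 participants (48 per group) is needed for an 80% probability" to find a difference between the arms.
- Effect: "we hypothesized a standard mean difference of between 0.36 and 0.52, between the treatment and control group".
- Test: the trial "will use an ANOVA and t-test (alpha error level = 5%, two-sided) for independent samples".
- Result: "Given these effect estimates, with an alpha of 0.05, an 80% power, and a 20% attrition, we estimated a sample size of approximately 96", that is, 48 per group. Attrition is listed among the inputs, so 96 is the number randomised.

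Section 2.1 gives 1:1 allocation. Section 2.12 (Statistical Analysis) plans a two-way mixed ANOVA (Condition × Time). It analyses participants who attended at least one session, using baseline and their last available assessment. Section 2.9 and Table 1 show that the control arm is assessed only at weeks 0 and 12. Section 2.11 reports pilot data on 14 client cases, "which included 10 completers and 4 early dropouts".

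**The concern.** An SMD near 0.5 with 80% power at two-sided 5% needs roughly 60 per arm before any allowance for attrition, and a smaller SMD needs many more. A total of 96 that already includes 20% attrition is therefore too small for any effect in the stated range. This is a stated result that does not follow from inputs stated beside it, so it is not a matter of detail left to a fuller document.

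The figure is the trial's main quantitative justification. If power is in truth between one third and three fifths, a non-significant result is a likely outcome even when the therapy works as hypothesised. A report citing 80% power would invite readers to take that result as evidence against the effect. Section 1.1 says that no adapted CBT treatment specific to racial trauma yet has randomised evidence of efficacy, so this first result would carry weight.

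**Working it through.** **Inputs.** Two-sided α = 0.05, power 80%, SMD d = 0.36 to 0.52, attrition 20%, N = 96 and the independent-samples test are from section 2.2. The 1:1 allocation is from section 2.1. On the standardised scale SD = 1.

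**Step 1. Try to reproduce 96.** By the normal approximation, n per arm = 2(1.960 + 0.842)²/d² = 15.70/d².

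- d = 0.52: 15.70/0.2704 = 58.1, so 59 per arm.
- d = 0.36: 15.70/0.1296 = 121.1, so 122 per arm.

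The noncentral-t calculation, which matches the named t-test, gives 59.03 and 122.1, so 60 and 123 per arm. Dividing by 1 − 0.20:

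| SMD | Evaluable per arm | Randomised per arm | Total randomised |
|---|---|---|---|
| 0.52 | 60 | 60/0.8 = 75 | 150 |
| 0.36 | 123 | 123/0.8 = 153.75, so 154 | 308 |

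The stated 96 falls short by 54 to 212 participants.

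**Step 2. Other routes to 96.** None keeps the stated inputs.

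- One-sided 5%, d = 0.52, no attrition: 46.4 per arm, so 47, or 94 in total. This is the closest match, but it contradicts both the two-sided test and the 20% attrition.
- One-sided 5%, d = 0.36, no attrition: about 96 per arm, not 96 in total.
- Inflating by multiplying by 1.2 instead of dividing by 0.8: 60 × 1.2 = 72 per arm, or 144 in total, at d = 0.52.
- d = 0.65 with 20% attrition: 96 to 98 in total, but 0.65 lies outside the hypothesised range.

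**Step 3. Power at the stated size.** Evaluable per arm after attrition: 96 × 0.8/2 = 38.4, about 38. Power comes from the noncentral t distribution with 2n − 2 degrees of freedom and noncentrality d√(n/2). For n = 38 the noncentrality is 0.36 × √19 = 1.57 and 0.52 × √19 = 2.27.

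| Evaluable per arm | Power, SMD 0.36 | Power, SMD 0.52 | SMD with 80% power |
|---|---|---|---|
| 38 (20% lost) | 34% | 61% | 0.65 |
| 48 (none lost) | 42% | 71% | 0.58 |
| 34 (pilot dropout) | 31% | 56% | 0.69 |

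At the midpoint, SMD 0.44, power with 38 per arm is 47%. The last row uses the pilot's 4/14 = 29%: 96 × (10/14)/2 = 34.3 per arm.

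**Step 4. Does the mixed ANOVA change this?** The control arm has two assessments, so the between-arm Condition × Time test is equivalent to a t-test on change scores. With equal variances at both times and pre-post correlation ρ, the effective standardised difference is d/√(2(1 − ρ)). For baseline-adjusted ANCOVA it is d/√(1 − ρ²). Setting these equal to the SMD that has 80% power at about 38 per arm gives the correlation required:

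| Analysis | ρ needed, SMD 0.52 | ρ needed, SMD 0.36 |
|---|---|---|
| Change score (two-point ANOVA) | 0.68 | 0.85 |
| ANCOVA | 0.60 | 0.83 |

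At an assumed ρ = 0.5, √(2(1 − 0.5)) = 1, so the change-score analysis has exactly the t-test's power, 34% to 61%. At an assumed ρ = 0.6, ANCOVA gives about 50% at SMD 0.36 and 80% at SMD 0.52. The article gives no value of ρ.

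**The case against.** **Attrition need not remove people from the analysis.** The last-available-assessment rule in section 2.12 keeps some dropouts, so 38 per arm is the pessimistic end. This is fair. Full retention, however, gives only 42% to 71%. A control participant who drops out also has no assessment between baseline and week 12, so the value carried forward is baseline, which may itself alter the estimated effect.

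**The main model is the ANOVA, not the t-test.** Section 2.2 names both. At SMD 0.52 with full retention, a pre-post correlation of about 0.60 brings the two-point interaction to 80%, and about 0.44 does so for ANCOVA. Such values are not extreme, and a condensed article may leave the correlation to the full protocol. The top of the range could therefore be defended under an added assumption. The bottom could not without a change-score correlation of about 0.81 to 0.85. Section 2.2 also describes the calculation as resting on means, standard deviations and a clinical cut-off, with no mention of a correlation.

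**The pilot says little about attrition.** Four of 14 has an exact 95% interval of about 8% to 58%, which includes 20%. The pilot was not quite complete, its dropout is from treatment and not from outcome assessment, and the trial adds retention measures. This stands: the 29% is a reason to show a sensitivity figure, not proof that 20% is wrong. The main finding does not depend on it.

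**Other repairs exist.** A different effect size, a stated correlation or a larger N would also remove the contradiction. That is true, and it concedes that the present text cannot stand.

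**Conclusion.** The concern holds. On the article's own inputs, 80% power needs 150 to 308 randomised, not 96. With 96 randomised, the named independent-samples t-test has 34% to 61% power if all 20% attrition is lost to analysis, and 42% to 71% if nobody is lost. The SMD with 80% power is 0.65 or 0.58 respectively, both above the hypothesised range.

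These figures assume a common SD, equal loss in the two arms and the SMD read as the between-group difference at end of treatment, as section 2.2 words it. The gain from using baseline scores is conditional on a correlation that the article does not state. A plausible value could bring the upper end of the range to 80%, but the lower end would need about 0.8 or more. The power statement is wrong as written and should be corrected before the trial relies on it.

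**What to change.** Restate the sample size paragraph of section 2.2, keeping N at 96. Suggested text: With 96 randomised and 20% attrition, about 38 participants per arm are evaluable. A two-sided 5% independent-samples t-test then has 80% power for an SMD of 0.65; power for SMDs of 0.36 to 0.52 is 34% to 61% (42% to 71% if no participant is lost).

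If the primary comparison is to be a baseline-adjusted ANCOVA or the Condition × Time test, say so in section 2.2 and give the assumed correlation between baseline and week 12, its source, and the resulting power at both ends of the SMD range. At an assumed 0.6, ANCOVA gives about 50% and 80%.

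Add one sensitivity line at the pilot's 29% dropout (about 34 per arm, t-test power 31% to 56%), noting that it rests on 14 cases.

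Cost: wording only, with no additional participants or assessments. The price is a less favourable power statement. If the sponsor wants to keep the 80% claim for the stated SMD range and the t-test, the number randomised has to rise to the 150 to 308 shown above.
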